## Abstract

**Background:**

A variety of household chores expose women to a variety of biomechanical and psychosocial risk factors. A result of this is many housewives with musculoskeletal disorders. Given the interactive effects of these risk factors, it is necessary to consider multiple strategies to mitigate their effects. Accordingly, the present study will investigate the impact of a health promotion training program based on a participatory ergonomic approach towards a reduction in the prevalence of musculoskeletal disorders and an improvement in the quality of life of housewives.

**Methods:**

Iranian housewives aged 20–65 years currently attending a specialist health clinic due to a painful musculoskeletal complaint will be invited to join the study. Recruitment will continue until a sample of 160 women provides informed consent to participate. The study will be conducted using a mixed-methods protocol in two phases. In the first phase, psychosocial and biomechanical risk factors will be identified using a qualitative approach. In the next phase, the results from the qualitative approach will be used to develop a conceptual framework based on health promotion theories and an intervention program based on a participatory ergonomic approach designed. Participants will be randomly allocated into one of four groups: (1) biomechanical intervention group, (2) psychosocial intervention group, (3) multidisciplinary intervention group (both biomechanical and psychosocial intervention), and (4) a control group. Data will be collected using Rapid Entire Body Assessment (REBA), Visual Analog Scale (VAS), Work Ability Score (WAS), Hospital Anxiety and Depression Scale (HADS), and the 36-item Short-Form health survey (SF-36) at baseline in 3-month and 6-month follow-up assessments. The impact of the three interventions on musculoskeletal disorders, work ability, stress, and quality of life will then be evaluated.

**Discussion:**

The study will provide a practical approach to reducing stress, reducing musculoskeletal disorders, enhancing the ability to work, and improving the quality of life of women with musculoskeletal disorders associated with housework. If the designed interventions in the present study are effective, they will have the great practical potential for generalization to all housewives.

**Trial registration:**

ClinicalTrials.gov IRCT20200602047640N. Registered on 07 September 2020 with the IRCTID.

## Background

Many people have to engage in physical work to meet their personal and social needs. Whilst this work may promote their health and social development across both social and economic fields, it may also involve encountering various risk factors which, in turn, can lead to health problems [1, 2]. Work-related musculoskeletal disorders (WMSDs) are one of the most important of these health problems. These disorders are very common in both industrialized and developing countries, with statistics showing that nearly 150 million people worldwide are affected [3]. WMSDs cause pain and may lead to inability to perform physical activities, decreased functional capacity, weakness, and loss of individual independence. A consequence of all of these impairments is low health-related quality of life (HRQOL) [4].

WMSDs are multifactorial phenomena, and multiple biomechanical and psychosocial risk factors can contribute to their occurrence [5–7]. Similarly, the presence of various risk factors in work environments has indicated potentials for an interactive effect which can aggravate the impact of these risk factors on the occurrence of WMSDs [8, 9]. Therefore, it can be appreciated that intervention programs and measures that focus on the simultaneous control of these risk factors will be more effective in preventing these disorders than interventions that address these risk factors separately [10].

Housework is one of the most pressing jobs for women, and the risk of WMSDs is very high due to the presence of multiple risk factors associated with it [11–13]. Housework by itself may be a risk factor for WMSDs among women, and most importantly, these disorders limit women’s ability to protect themselves from its effects. Housework in unfavorable conditions, as well as potentials for stress caused by a high workload, can lead to more musculoskeletal problems and interfere with the healing process [14]. Studies have shown that housekeeping activities require twice as much energy as many other jobs and that various tasks routinely performed by a housewife could lead to stress and WMSDs [15].

The prevalence of musculoskeletal disorders in housewives is reported as 53% in Iran [16, 17], 49% in India [18, 19], and 84% in Bangladesh [20]. A review study by Habib and colleagues in Lebanon found that the biomechanical activities undertaken in the home increases the incidence of back, neck, and shoulder pain in housewives [4]. This being so, implementing preventive intervention programs for housewives is very important.

Women’s housework typically includes cooking, cleaning, washing, shopping, and caring for family members and children, all of which requires considerable time and involves physical, emotional, and mental activities. Altogether, these impose a high biomechanical and psychological burden on them [21, 22]. Similarly, a relatively recent study by Tavafian et al. showed that Iranian women do heavy household chores in poor physical conditions and in unfavorable psychosocial situations, which exacerbated their participant’s low back pain [23].

Despite numerous WMSD disorders in Iranian housewives, our review found that there has been no research-based intervention to reduce or control the biomechanical and psychosocial risk factors associated with WMSDs in Iranian housewives. It is the case that most studies have focused on formal work environments. In addition, few studies have examined the simultaneous effects of biomechanical and psychosocial interventions on reducing musculoskeletal disorders. Moreover, according to our review, there have been no special intervention studies for housewives in other countries either. Nevertheless, housework activities, due to their high physical and mental burden, expose housewives to WMSDs, especially in the lower back, neck, and shoulders [23, 24]. Therefore, biomechanical and psychosocial burdens of housework activities should be studied comprehensively from an ergonomics perspective, and appropriate risk reduction-based interventional programs and measures should be implemented to control or reduce these risk factors. Accordingly, using a qualitative approach, the present study will attempt to identify biomechanical and psychosocial risk factors related to WMSDs among Iranian housewives. Then, a health promotion intervention program will be implemented based on a participatory ergonomic approach towards improving the HRQOL of a sample of housewives with WMSDS symptoms, and the effectiveness of the program will be examined.

Based on the literature, it is presumed that this training interventional program will improve the HRQOL and work ability of housewives, and also that the severity of WMSDs and stress will be improved in the intervention groups relative to the control group. We also hypothesize that the use of a mixed biomechanical and psychosocial risk reduction interventional program will have an additive effective and this program will be more effective than each of the two separate intervention programs to reduce WMSDs and stress and improve the HRQOL and work ability consequences.

## Methods

### Aim, design, and outcomes

The aim of this study is to provide a practical approach to reducing musculoskeletal disorders, reducing stress, enhancing the ability to work, and improving the quality of life of women with musculoskeletal disorders associated with housework. The study will use an exploratory sequential mixed-methods design.

### Primary outcomes

The selection/development of a health education and health promotion model based on the results of an initial qualitative studyThe design of health promotional interventions based on the results of previous steps (qualitative step)

### Secondary outcomes

The effect of our educational intervention on the quality of life, ability to work, stress, and musculoskeletal problems.

Accordingly, the main research questions addressed in this study are as follows:
Which health education and health promotion model will be preferred for use among the housewives?We are testing three interventions: which intervention is the most effective for improving quality of life and work ability, and reducing WMSD symptoms and stress?

### Ethical approval

The study protocol has been approved by the Medical Ethics Research Center of Tarbiat Modares University (reference: IR.MODARES.REC.1398.038). All participants will be provided with full information of their part in the study and assured that their information will be kept strictly confidential. All participants will be asked to complete a written informed consent form. This will provide a clear understanding that their participation is entirely voluntary, and they have a right to withdraw at any time during the study.

### Participants

The research population will comprise full-time housewives aged 20–65 years with a diagnosed MSD disorder. To meet these inclusion criteria, recruitment will be from women currently attending a specialist health clinic in Iran due to a painful musculoskeletal complaint. Invitations to join the study will continue to be offered to every eligible woman until we have achieved a sample of 160 housewives who provide informed consent to participate.

Full details of inclusion and exclusion criteria are provided in Table 1.

**Table 1 Tab1:** Inclusion and exclusion criteria

**Inclusion criteria**	
Working-aged woman aged 20–65 years	
Diagnosed MSD and an MSD pain intensity score of 4 and higher based on the visual analog scale (VAS) [25, 26].	
The motivation and willingness to fully participate with any randomly allocated intervention	
Being married and living with the family	
Having no job other than housekeeping	
Not pregnant, nor breastfeeding	
**Exclusion criteria**	
Not able to actively attend the training sessions	
Diagnosis of a congenital disease that can affect skeletal tissue	
Having a child under 2 years of age	
Becoming pregnant during the study	
The occurrence of an event or accident that does not allow the person to complete the whole study procedure	
Taking medication to treat a mental illness	

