### The intervention programs

The conceptual framework of the health promotion model will be developed based on phase 1 findings from the qualitative study. Recruitment of women who meet the inclusion criteria will continue until the required sample size is achieved. At this point, all participants will be coded and blindly allocated into one of four intervention groups by the researchers using a permuted block randomization program: (1) biomechanical, (2) psychosocial, (3) multidisciplinary (biomechanical and psychosocial), or (4) control. Based on the design of the randomized controlled trial intervention, the impact of the different intervention programs on musculoskeletal disorders, work ability, and quality of life of the housewives will be evaluated. As shown in Fig. 1, measures will be collected at baseline, after 3 months, and after 6 months of following their respective program.

To implement the content of the three intervention programs, a participatory ergonomic approach will be used. The effectiveness of this approach in ergonomic interventions depends on the ability and active cooperation of participants [29]. The required training content for participants in the psychosocial intervention will be provided following the conceptual framework developed in the qualitative study and the resulting theory. Similarly, for participants in the biomechanical intervention group, the required training will be provided following the conceptual framework derived from the qualitative study and job safety analysis (JSA) method. Finally, the multidisciplinary intervention group will receive the training provided to the psychosocial and biomechanical groups: that is, they will do both interventions. The multidisciplinary groups will receive both of the other two interventions in full.

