### Data analysis

#### Phase 1

To perform the process of qualitative content analysis, the audio file of each interview will be listened to attentively several times on the same day and it will be transcribed verbatim. To keep the data from the interviews confidential, a code will be assigned to each transcript. To come up with a general impression of the interviews and become fully immersed in the data, the audio files of the interviews and the transcripts will be reviewed several times, and any possible ambiguities and inconsistencies will be removed by comparing the audio files and the transcripts. The interviews will be audiotaped and a summary of the key issues in each interview will be then sent to each participant to ensure that the researcher will have accurately interpreted that participant’s comments (a “member check”) [26]. The process of data analysis will be performed continuously and simultaneously with the data collection process. All words, sentences, and paragraphs that are related in the analysis process will be considered as a single semantic unit. After merging the semantic units, the codes will be extracted. The codes together form the subcategories and then the main categories. Finally, upon the abstraction of the categories, the relevant themes will be identified. MAX.QDA software will be used to manage the data [40].

#### Phase 2

The collected data will be analyzed with SPSS software using descriptive statistics (including frequency, frequency percentage, mean, and standard deviation) and inferential statistics. We will undertake both “intention to treat” and “per protocol” approaches to the inferential statistical analyses to achieve fully understand the outcomes and manage bias in the face of any drop out. To compare the differences between the values obtained before the intervention and 3 and 6 months after the intervention in each group, generalized mixed models of analysis of variance for repeated measures will be used. We will also calculate differences between means of the independent groups with their respective 95% confidence intervals. All tests will be performed at a significance level of 0.05 (p <0.05). The Kolmogorov-Smirnov test will be used to test the normality of the data. The per protocol analyses will only include the participants who complete the intervention to which they were allocated.

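### Two exclusion criteria in Table 1 are not limited to the time before randomisation and so conflict with the intention-to-treat analysis, beside which an unranked completers-only analysis is planned

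*Protocol article*

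**What the plan says.** The exclusion criteria in Table 1 of the protocol article include "Becoming pregnant during the study" and "The occurrence of an event or accident that does not allow the person to complete the whole study procedure". Pregnancy at entry is dealt with separately, by the inclusion criterion "Not pregnant, nor breastfeeding".

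Under The intervention programs, allocation follows the completion of recruitment: "At this point, all participants will be coded and blindly allocated into one of four intervention groups". Training and the 3- and 6-month assessments come after that. The same section gives the multidisciplinary arm both programmes in full. Control women are offered a programme only after the final evaluation.

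Under Data analysis, Phase 2, the article states: "We will undertake both “intention to treat” and “per protocol” approaches to the inferential statistical analyses". One stated purpose of using both is to "manage bias in the face of any drop out". The completers' set is defined as follows: "The per protocol analyses will only include the participants who complete the intervention to which they were allocated". The article does not name either analysis as the main one. It also does not say whether a woman who meets one of the two criteria after allocation is still followed and kept in the ITT set.

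**The concern.** An exclusion criterion decides who may enter a trial. An event during follow-up cannot do that for a woman already randomised; it can only take her out. If she is taken out, the groups compared are no longer the groups that were randomised, and the analysis is not ITT whatever its label.

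The second criterion is also open-ended. Many kinds of dropout could count as an event that prevented completion, so a woman lost to follow-up could be recorded as excluded and leave the denominator.

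The per-protocol set adds a second selection on what happens after allocation. Completing the allocated intervention means two programmes in one arm, one programme in each of two arms, and nothing definable in the control arm during follow-up. The filter therefore cannot work alike in the four arms, and it bears on the hypothesis that the combined programme is the most effective. With two unranked analyses, nothing in the article settles which one carries the conclusion if they disagree.

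**Working it through.** **Step 1. When can the two criteria apply?** Pregnancy at entry is already screened by an inclusion criterion, so the exclusion entry adds something only for pregnancies after entry. Allocation takes place once recruitment is complete, and follow-up then runs for 6 months. Trial status puts recruitment from November 2020 to April 2021, so an early recruit could wait about five months between consent and allocation. An event in that wait is before randomisation and excluding for it is harmless. An event in the 6 months of follow-up is after randomisation. The wording covers both periods.

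**Step 2. Set against the analysis.** ITT needs every randomised woman, in her allocated arm. Table 1 as written excludes some of them. No sentence in the article reconciles the two.

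**Step 3. The plan's own figures** (Sample size and power calculations: SDs 20.2 and 21.1, difference 15, multipliers 1.96 and 0.84).

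- n = (1.96 + 0.84)² × (20.2² + 21.1²) / 15² = 7.84 × 853.25 / 225 = 29.7, which rounds up to the stated 30 per group (the printed 29.9 is a slip without effect).
- Pooled SD = √(853.25 / 2) = 20.65.
- The article recruits 40 per group, allowing for 30% dropout.

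**Step 4. Size of a possible bias, with no true effect.** Let a share p of an arm be removed, and let removed women score g points worse than those retained. If the full arm has mean 0 and the retained women mean m, then (1 − p)m + p(m − g) = 0, so m = p × g. With the same gap in both arms, the bias in the difference is (p₁ − p₂) × g.

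The article gives neither p by arm nor g. All values below are assumptions.

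| Removed, arm 1 vs arm 2 | Gap g | Bias (points) |
|---|---|---|
| 30% vs 0% | 0.3 SD = 6.2 | 0.30 × 0.3 × 20.65 = 1.9 |
| 30% vs 0% | 0.5 SD = 10.3 | 0.30 × 0.5 × 20.65 = 3.1 |
| 30% vs 10% | 10 | 0.20 × 10 = 2.0 |
| 5% vs 0% (2 of 40) | 0.3 SD | 0.05 × 0.3 × 20.65 = 0.3 |
| 5% vs 0% (2 of 40) | 0.5 SD | 0.05 × 0.5 × 20.65 = 0.5 |
| 30% vs 30% | any, equal | 0 |

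In the 30% vs 10% row, 28 and 36 women remain. The standard error is 20.65 × √(1/28 + 1/36) = 5.20, and a bias of 2.0 raises the two-sided error from 5% to about 6.7%. If removed women would have scored better, the sign reverses.

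**Step 5. Effect of the fix on power** (normal approximation, difference 15, SD 20.65). Power is 80.3% with the planned 30 per arm, 90.1% with outcomes for all 40, and 77.6% with the 28 left after 30% loss. The 90.1% assumes that the 15-point difference is not diluted by women who stopped the programme.

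**The case against.** The strongest reply is that the two entries may be reasons for discontinuation that ended up in an eligibility table. The article commits to ITT and nowhere says that these women lose their assessments or leave the ITT set. A full protocol or SAP may define the sets and rank them. That is fair, and it is why the point is a conflict in wording and not proof that women will be dropped. But Table 1 calls these events exclusions without limiting them in time, and an unseen analysis plan would not recover outcomes that were never collected. Reporting a completers' analysis beside ITT is ordinary practice, and the article offers the two together, not per protocol alone, as the way to handle dropout. What remains is that completion has no common meaning across these arms.

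Three stronger readings are tempting, and the documents do not support them.

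- A reader might count "Not able to actively attend the training sessions" as a further post-randomisation rule that can bite only in the trained arms. It reads naturally as a baseline screen, in line with the inclusion criterion on willingness to take part in whichever intervention is allocated.
- A reader might infer that removal will differ by arm and favour the programmes. Pregnancy and accidents have no evident link to arm. The Discussion expects low attrition in all training groups, though it accepts that time commitment differs between them.
- A reader might apply the whole 30% dropout allowance and set the effect in completers against the effect in all randomised women. That contrast arises in any trial with such dropout and does not measure what the two Table 1 entries do.

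**Conclusion.** The conflict stands on the text: two exclusion criteria reach past randomisation, and applied as written they remove randomised women from a trial that promises ITT. The unranked completers-only analysis is a second, related weakness, because its filter works differently in arms with no, one and two programmes.

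The size is not known. The 1.9 to 3.1 points, about 12% to 21% of the planned 15 (1.9/15 and 3.1/15), require 30% removed from one arm and none from the other, which is 12 of 40 women, and an assumed gap of 0.3 to 0.5 SD. Pregnancies and accidents alone may well remove fewer; at 2 of 40 in one arm the same gaps give 0.3 to 0.5 points. Balanced removal with equal gaps gives none. The article does not name the instrument to which the 15 points belong, so these figures are on the scale of the sample-size formula only.

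This should be fixed because it is cheap to do before follow-up ends and cannot be repaired afterwards. It does not show that the trial's results would be invalid.

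**What to change.** - In Table 1, limit the exclusion criteria to status before randomisation, and say that the pregnancy and event-or-accident entries apply only up to allocation.
- After allocation, treat these events only as recorded reasons for not continuing the programme. Whether a woman continues is for the investigators.
- State that her 3- and 6-month outcomes are still sought and that she is analysed in her allocated arm.
- Under Data analysis, Phase 2, base conclusions on the ITT analysis and label the per-protocol analysis supportive. Define completion for each arm, including what it means for control women.

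The cost is a few sentences of protocol text and some extra follow-up contact. The recruitment target does not change. The downside is a possibly diluted effect estimate, since women who stopped the programme stay in the comparison.

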### Study design

This exploratory sequential mixed-methods study will be conducted in two phases, each of which is described below. The schedule of enrolment, interviews, intervention, and assessment is shown in Table 2. This protocol was developed and reported according to the recommendations of the Standard Protocol Items: Recommendations for Interventional Trials (SPIRIT), and the clinical trial will be conducted and reported following the Consolidated Standards of Reporting Trials (CONSORT).

